#### Training of peer educators (intervention arm)

Barbers, stylists, and leaders in faith-based communities are influential peers who are uniquely positioned to administer the proposed health education program [60, 61]. With adequate training and supervision, we expect that they will be able to utilize motivational enhancement techniques (the trans-theoretical change model) leading to the desired behavior, namely seeking OSA evaluation and adhering to treatment. These techniques have proven effective in a similar project that aimed to improve blood pressure control among blacks in community settings [62, 63]. As indicated in Fig. 4, the conceptual framework for training educators is modeled after Behavior Change Communication best practices and recommendations [64, 65]. Peer health educators are taught how to deliver tailored motivational sessions depending on where an individual is on the Stages of Change model (e.g., pre-contemplation, contemplation, preparation, action, maintenance, relapse prevention), which will be determined by baseline survey on Stages of Change [66]. For our current study, health educators will apply for the health educator job and will then be interviewed by the project manager and coordinator. To be considered for the peer health educator position, individuals have to meet the following qualifications: (1) previous experience working/volunteering with programs or organizations that tackle health or social issues in black communities; (2) knowledge of community resources and organizations in Brooklyn, Bronx, Queens, and/or Staten Island; (3) available to work evenings and weekends regularly; (4) ability to juggle priorities and manage time productively; (5) effective oral and written communication skills; (6) energetic open-minded people-person; (7) flexible, ability to change gears at a moment’s notice and ‘go with the flow’; (8) thrives in a fast-paced environment; (9) highly organized, pays attention to detail, and can follow strict protocols; (10) creative problem-solver; (11) comfortable using a computer (Word, Excel, Access, Outlook); and (12) a minimum of a high school education or GED. Peer health educators will not be required to have previous training or expertise in medicine or health training. Health educators will have a maximum case load of 3–4 participants at a given time and will provide support and counseling for each participant for 10 sessions.

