#### Sample size and power analysis

We plan to screen approximately 1250 blacks in the community. Assuming 39% of blacks are at risk for OSA, we propose to enroll 398 men and women (199 per study arm). With a 35% attrition rate, 258 will have provided adherence data during 6-month follow-up assessment. Based on the pilot data, we expect that 41% in the intervention arm (*n* = 82) and 26% in the attention-control arm (*n* = 52) will have completed all aspects of the trial, including site interview, home evaluation, and follow-up assessment (Fig. 2).

The primary study outcome is receipt of home OSA evaluation after tailored peer-based sleep health education. Data obtained from a sample of blacks provided a current estimate of the likely OSA evaluation rate we expect in the partner community. Analysis showed that 41% of participants adhered to recommended OSA evaluation after intervention exposure, whereas 26% of participants in a control group agreed to undergo evaluation. These preliminary findings represent the likely adherence rates expected in our proposed study.

We propose to achieve an evaluation rate in our intervention arm of 41% based our pilot study mentioned above. This would represent a 63% greater adherence rate compared with controls, which potentially would have a significant public health impact. Assuming a 15% increase in the likelihood of undergoing home-based OSA evaluation, a standard error of 0.09% and a sample size of 398, the study will be adequately powered (> 85%) to detect a significant increase in adherence. Specifically, an observed difference of 15% would be reported with a 95% CI 7–24%. A two-tailed test, with 80% power and α = 0.035 comparing adherence rates of 26% with 41% requires 199 participants per group. Of note, our sample size estimate adjusted for potential intra-cluster coefficient that may be observed in both the treatment and control arms, which according to our initial pilot was 0.014. The resulting effective sample size (*ESS = [M x K/DE]*) after adjustment for design effect (*DE*)… [*DE = 1 + (n-1)ρ*] was *n* = 398 (199 participants per arm) [97, 98]. The study is also powered to assess differences in adherence rates to CPAP treatment between the two arms considering the likely attrition rate of 35% during follow-up assessment.

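### 398 is given both as the number enrolled and as the effective sample size after the clustering adjustment; with an ICC of 0.014 both can be true only if the design effect is 1

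*Protocol article*

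**What the plan says.** All the figures are in the protocol article, section Sample size and power analysis, unless noted.

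- Enrolment: "we propose to enroll 398 men and women (199 per study arm").
- Requirement: "A two-tailed test, with 80% power and α = 0.035 comparing adherence rates of 26% with 41% requires 199 participants per group".
- A second power statement, which names no alpha: "a sample size of 398, the study will be adequately powered (> 85%) to detect a significant increase in adherence".
- Clustering: the authors say "our sample size estimate adjusted for potential intra-cluster coefficient that may be observed in both the treatment and control arms", with a coefficient "which according to our initial pilot was 0.014".
- Formulas: effective size ESS = M × K / DE, with design effect DE = 1 + (n − 1)ρ. No values are given for M, K, n or DE.
- Result: "The resulting effective sample size" after this adjustment is 398, or 199 per arm.

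The only figure in the article that bears on cluster size is in the section on training of peer educators: "Health educators will have a maximum case load of 3–4 participants at a given time". That is a ceiling at one moment, not a total per educator over the trial.

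**The concern.** An effective sample size is the number of independent observations that carry the same information as the clustered sample. With a positive intra-cluster coefficient and more than one participant per cluster, it must be smaller than the number enrolled. Here the two are identical, although the section says an adjustment was made and prints the formula for it.

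Read as printed, the section says that 398 independent observations remain after the allowance for clustering. That overstates the information for the main contrast. It also leaves unclear what the stated power refers to, because the same 398 supports both an 80% statement and an above-85% statement. The effective size matters in this trial: the analysis section chooses GEE because it handles clustering, and the limitations section warns that inference suffers if the sample is too small.

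**Working it through.** **Inputs (all from the sample-size section).** Enrolment 398 (199 per arm); rates 26% and 41%; two-sided alpha 0.035; power 80%, and separately above 85%; ρ = 0.014. Cluster size n is not stated and has to be assumed.

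**Step 1: try to reproduce the stated effective size.** Setting M × K to the enrolment, 398 / DE = 398 requires DE = 1. Then 1 + (n − 1) × 0.014 = 1 gives n = 1. The stated figure is reproduced only with one participant per cluster.

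**Step 2: effective size for assumed cluster sizes.** ESS = 398 / [1 + (n − 1) × 0.014]. Power is for the pooled two-proportion test with m = ESS / 2 per arm:

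power = Φ{[0.15 √m − z √(2 × 0.335 × 0.665)] / √(0.26 × 0.74 + 0.41 × 0.59)}, with z = 2.108 for alpha 0.035.

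| Assumed n | DE | ESS | Power, alpha 0.035 | Power, alpha 0.05 |
|---|---|---|---|---|
| 1 | 1.000 | 398 | 85.9% | 89.0% |
| 3 | 1.028 | 387 | 84.9% | 88.1% |
| 4 | 1.042 | 382 | 84.4% | 87.7% |
| 10 | 1.126 | 353 | 81.3% | 85.1% |
| 12.7 | 1.164 | 342 | 80.0% | 83.9% |
| 25 | 1.336 | 298 | 74.0% | 78.6% |

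All rows are before the 35% attrition. The overstatement of ESS equals DE − 1: 2.8% at n = 3 and 33.6% at n = 25.

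**Step 3: check the 80% statement.** With independent observations, the requirement per arm for 26% against 41% at two-sided alpha 0.035 and 80% power is:

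- pooled: [2.108 × √0.44555 + 0.842 × √0.4343]² / 0.15² = 171.1
- unpooled: 0.4343 × (2.108 + 0.842)² / 0.15² = 168.0
- pooled with continuity correction: (171.1 / 4) × [1 + √(1 + 4 / (171.1 × 0.15))]² = 184.2

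None of these is 199. Some inflation is needed to reach 199, which fits 398 being an inflated enrolment.

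**Step 4: check the above-85% statement.** At alpha 0.035, 199 independent participants per arm give 85.9%. Power is already just under 85% at n = 3. At that alpha the statement fits 398 with essentially no clustering. If alpha 0.05 was meant, it also holds with clusters of up to about 10.

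**Step 5: can the design effect be recovered by working backwards?** Dividing 199 by the rounded requirement gives different answers for different formulas:

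| Formula | Per arm | DE = 199 / per arm | Implied n | Implied ESS |
|---|---|---|---|---|
| Pooled | 171 | 1.164 | 12.7 | 342 |
| Unpooled | 168 | 1.185 | 14.2 | 336 |
| Continuity-corrected | 184 | 1.082 | 6.8 | 368 |

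The implied ESS is simply twice the unclustered requirement, so this is a reconstruction and not a check of the formula.

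**Step 6: what a true effective size of 398 would take.** Enrolment would have to be 398 × DE: about 409 at n = 3, 415 at n = 4 and 463 at n = 12.7. The article plans 398.

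**The case against.** The best defence is that this is one loose term in a condensed article. The section says the estimate was adjusted for the coefficient. If 398 is the inflated enrolment, the trial may be sized correctly for 80% power after clustering. The values of M, K and n may stand in the full protocol, and clustering is handled in the analysis by GEE. This largely stands: leaving out the inputs is not itself a fault, and nothing here makes the planned test invalid. It does not rescue the printed result, because a formula and a positive coefficient are followed by a number that they cannot produce for any cluster larger than one.

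A second objection is that the cluster is not identified. The analysis section discusses educator assignment, while the data-management section also plans to examine site effects. The caseload of 3–4 is a maximum at one time. This also stands, and it is why no single cluster size can be used. It does not point to clusters of one: educators may carry several participants at a time, and participants are recruited at shared venues.

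A third is that the above-85% statement names no alpha and may have been made at 0.05. Step 4 allows for that, so the statement cannot be called wrong on its own. It cannot be reconciled with the 80% statement until alpha and effective size are given.

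A reader might also infer that the section's own formula and coefficient give an effective size of about 342. They do not, because the formula also needs a cluster size. The value 342 comes from choosing the pooled test and solving backwards, and the other two standard formulas give 336 and 368.

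**Conclusion.** The point holds as an internal contradiction. Under the section's own formula, 398 cannot be both the enrolment and the effective sample size unless the design effect is 1. Two explanations remain: 398 is the inflated enrolment under the wrong label, or the adjustment was not carried through. The 80% statement leans towards the first. The above-85% statement, if made at alpha 0.035, leans towards the second.

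The size of the error depends on an assumption that the article does not supply. For clusters of 3 to 25 and ρ = 0.014, the effective size runs from about 387 down to 298, and power at alpha 0.035 from about 85% down to 74%, against 85.9% without clustering. These figures assume equal clusters in both arms and the pooled test, and they precede attrition.

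Two stronger conclusions are tempting but not supported. One is that all the figures form a single consistent chain (171 per arm, design effect 1.16, 12.7 participants per educator); this is one possible reconstruction, and it leaves the above-85% claim unexplained at alpha 0.035. The other is that clustering leaves the trial short of participants; if 398 is already the inflated number, the enrolment may be adequate for 80% power before attrition.

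**What to change.** Rewrite the clustering sentence and the two power statements in the sample-size section so that they:

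1. state that 398 (199 per arm) is the number enrolled;
2. say what the cluster is, and give the cluster size and design effect actually used with ρ = 0.014;
3. report the resulting effective sample size, which will be below 398, and say whether it is before or after the 35% attrition;
4. restate the 80% and above-85% statements so that both refer to that effective size and to the same alpha.

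The cluster size and design effect must come from the sponsor's own calculation. The back-solved values (171 per arm, 1.16, 12.7) should not be written in as if they were the plan's figures. The cost is a few lines of text. Enrolment, randomisation and analysis do not change; the stated effective size becomes less favourable, and one of the power statements may too.

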#### Statistical analysis plan

To describe sample characteristics, we will use measures of central tendencies and dispersion for continuous data; frequency distributions will be used for categorical data. We will use χ^2^ tests to compare categorical data and GEE to examine relationships between predictors of adherence to OSA evaluation and/or treatment. The main dependent measure will be adherence to OSA evaluation (yes vs. no) and adherence to CPAP treatment (yes vs. no). Effects of sociodemographic and clinical factors will be adjusted. MANCOVA will be used to assess differences between baseline and 6- and 12-month subjective measures (e.g., self-efficacy, apnea knowledge, functional outcomes in sleep). Structural Equation Modeling will be used to examine the path toward adherence to OSA evaluation and/or CPAP treatment, considering the contributions of candidate factors.

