## Methods and design

In a two-arm, randomized controlled trial, we will ascertain effectiveness of peer-based sleep health education and social support in increasing OSA evaluation and treatment rates among 398 blacks at risk for OSA (198 participants in treatment group and 198 participants in attention-control group), over a 12 month period. Participants in the intervention arm will receive quality-controlled, culturally, and linguistically tailored peer education using a sleep health education manual developed based on principles of motivational enhancement. Participants in the treatment arm will each receive up to five peer-based sessions promoting OSA evaluation. Those with an OSA diagnosis will receive five additional peer-based sessions promoting OSA treatment compliance and adherence from a peer health educator contingent upon poor treatment adherence from CPAP-based reports. Those in the attention-control arm will receive standard OSA literature from the study staff. Regardless of group assignment, we will ascertain all outcomes at baseline and at 6- and 12-month follow-up assessments.

The study was approved by the New York University Langone Health Institutional Review Board and all participants will be consented by study staff before enrollment. The trial is in accordance to the Consolidated Standards of Reporting Trials (CONSORT) Statement on randomized trials for non-pharmacological treatment and the Standard Protocol Items: Recommendations for Interventional Trials SPIRIT checklist (see Additional file 1 for CONSORT Figure, SPIRIT Figure and checklist Figs. 2 and 3) [37, 38].

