The data manager will perform interim analysis to ensure that selection and attrition biases do not occur if refusal occurs after recruitment or randomization. Selection bias might result from participant’s refusal to participate and attrition bias could result in an unbalanced design. Appropriate statistical techniques, such as Heckman 2-stage approach (Generalized Estimation Equations (GEE) Probit Model) [90] and Monte Carlo (EM algorithm) [91] analysis, will be used to address such biases or problems that might result from missing data. Adequate statistical corrections will be made in final statistical analyses to increase the generalizability of findings. Sociodemographic data obtained from those who did not participate will be used to determine whether individuals who did not participate are similar to those in the study (selection bias). Likewise, baseline characteristics of those who withdrew from the study will be contrasted with completers to determine whether any attrition bias may have occurred. Site-specific effects (shops vs. salons vs. faith-based site) will also be examined. If these analyses reveal meaningful between-group differences, such characteristics will be treated as covariates. If we identify missing data in the analysis (e.g., logs, checklists, rapport), we will use Kelsey’s method strategies to remedy missing data [92]. Although we do not plan to perform extensive cost-benefit analysis, we will document implementation costs (e.g., personnel, training costs, home visits, and postage and handling). In addition to performing analytical tests to minimize the potential confounding effects of missing data, we will engage in evidenced-based research design (recruitment and retention) strategies to minimize the possibility of missing data, some of which include (1) closely monitoring research milestones and targets and ensuring that participants reach these with the help of a health educator with whom the participants have a good rapport; (2) limiting the amount of research burden; (3) keeping close contact with participants through the project coordinator or health educator; and (4) providing adequate and fair monetary incentives for participating in the research study.

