
After the home sleep study, the study staff will provide the results to the study physician to determine the risk of sleep apnea from the WatchPAT™ home sleep recorder device. The study physician will discuss the home study results with all participants and will recommend treatment to those meeting OSA diagnostic criteria (AHI > 10). Participants who do not meet OSA diagnostic criteria will be transferred to the project coordinator either for study close-out since they no longer need to continue their participation in the study, for future clinic-based diagnostic assessment, or for treatment customization. Participants who are at risk for OSA will be referred for further diagnostic assessment and treatment to a sleep clinic accredited by the American Academy of Sleep Medicine. Expenses incurred from laboratory and CPAP procedures recommended by sleep clinicians in our catchment area will be billed directly to the participant’s insurance. In the rare instance that a participant might fail to obtain insurance, the study project will absorb some medical costs and a CPAP device will be dispensed as an in-kind contribution.

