##### Analysis

We will perform analysis on an intention-to-treat basis. We will assume participants in the intervention arm to have received the full intervention dose and those in the control arm to have received no tailored education. Prior to testing for intervention effects, we will verify comparability of the intervention and control arms with respect to all available sociodemographic data using *t* tests and χ^2^ tests. GEE methods will be used to estimate the odds associated with receipt of OSA evaluation contrasting the two study groups. GEE is preferred over standard logistic regression, as it adjusts for clustering effects. Delays in receipt of endpoint (OSA evaluation or treatment) will be adjusted in the models. Since the type of health educator may influence our findings, we will perform statistical analyses that will detect any potential confounding effect that health educator assignment may have on outcomes. This type of method is distinguishable from a traditional cluster randomized trial as the unit of randomization is at the individual/participant level and not groups of individuals.

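### The questionnaire outcomes are assigned to a MANCOVA worded as change from baseline, with no between-arm contrast and no link to the missing-data methods

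*Protocol article*

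**What the plan says.** The Statistical analysis plan section gives the questionnaire measures one sentence: "MANCOVA will be used to assess differences between baseline and 6- and 12-month subjective measures". Its examples are self-efficacy, apnea knowledge and functional outcomes in sleep. It does not mention study arm, an arm-by-time term or the role of the baseline value.

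The schedule covers both arms. Methods and design states: "Regardless of group assignment, we will ascertain all outcomes at baseline and at 6- and 12-month follow-up assessments". Exit interviews (Phase V) has every participant repeat the baseline questionnaires at 12 months.

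On loss to follow-up, Sample size and power analysis states: "With a 35% attrition rate, 258 will have provided adherence data during 6-month follow-up assessment". Data collection and management names a Heckman two-stage approach and says that "Monte Carlo (EM algorithm) [91] analysis, will be used to address such biases or problems that might result from missing data". It adds that "baseline characteristics of those who withdrew from the study will be contrasted with completers to determine whether any attrition bias may have occurred". Neither provision is attached to a named outcome or model.

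One further passage bears on who is followed. In Primary trial outcome: sleep home study, participants who do not meet the OSA criterion after the home study may be passed to the coordinator "for study close-out since they no longer need to continue their participation in the study". This is one of three possible dispositions.

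**The concern.** A randomised comparison asks whether the arms differ at follow-up. The MANCOVA sentence asks whether scores differ between baseline and follow-up. A shift common to both arms, from repeated testing, from regression to the mean or from information that everyone receives, would satisfy that test without any effect of peer education. A common shift is plausible here: under Attention-control group, controls also receive OSA literature and advice to seek home evaluation.

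The contrast matters beyond description. The Tertiary aim treats OSA knowledge and self-efficacy as mediators of peer education. That pathway presupposes an arm effect on those scales, which a pre/post test does not supply.

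The second issue is the method's handling of incomplete data. A standard MANCOVA on the 6- and 12-month values needs both for each participant and scale. Someone with only one follow-up visit contributes nothing unless values are imputed, and the article does not say that its missing-data methods feed this analysis.

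**Working it through.** **1. The plan's own figure.** Inputs from Sample size and power analysis: 398 enrolled (199 per arm), 35% attrition. 398 × (1 − 0.35) = 258.7, which agrees with the stated 258.

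**2. The contrast, side by side.** The Analysis text under Primary aim and outcome sets intervention against control for receipt of OSA evaluation, by GEE. The Analysis text under Secondary aim calls the CPAP analysis similar. The MANCOVA sentence is the only analysis statement for the questionnaire scales as outcomes, and its only named comparison is between time points.

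**3. What the literal wording would detect.** Assumptions, not from the documents: 258 participants (129 per arm), SD 1, baseline-to-follow-up correlation 0.5, a gain of 0.3 SD in both arms, no arm effect, two-sided α = 0.05. The SD of change is √(2 − 2 × 0.5) = 1. The expected test statistic for change is 0.3 × √258 = 4.82, so rejection is nearly certain. In 1000 simulated trials the baseline-to-follow-up test rejected in 1000. The baseline-adjusted arm comparison (ANCOVA) rejected in 53 (5.3%), close to its nominal level.

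**4. How many participants a complete-vector analysis could lose.** The documents give neither a 12-month loss nor a pattern of loss, so I show two cases. Both assume that 35% applies to the questionnaires.

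| Assumed pattern | Both visits | Exactly one visit |
|---|---|---|
| All loss by month 6, none later, no intermittent gaps | 398 × 0.65 ≈ 258 | 0 |
| 35% missing independently at each visit | 398 × 0.65² ≈ 168 | 398 × 2 × 0.65 × 0.35 ≈ 181 |

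The second row is a pessimistic illustration. Further loss between months 6 and 12, or occasional missed visits, would usually fall between the rows.

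**5. What that means for precision.** Illustration for one scale at one visit, in unadjusted SD units, ignoring clustering, two-sided α = 0.05, 80% power: detectable difference = (1.96 + 0.84) × √(2/n per arm).

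- 258 analysed (129 per arm): 0.35 SD; power for an assumed 0.3 SD difference, 67%.
- 168 analysed (84 per arm): 0.43 SD; power for 0.3 SD, 49%.

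In the first pattern both approaches use the same 258 participants with follow-up, so keeping partial responders gains nothing. In the second, a likelihood model would still use about 258 observed values at each visit, where the complete-vector MANCOVA would use 168.

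**The case against.** The strongest reply is that this is one condensed sentence in a journal article. A MANCOVA normally has a grouping factor, and in a two-arm trial that factor is naturally the arm. The article also commits to intention to treat: "We will perform analysis on an intention-to-treat basis". This stands in part. The sentence does not prove that no arm comparison is intended. However, the intention-to-treat statement sits under the primary aim, and the arm contrast is written out there but not for these scales. The one comparison that the sentence does name is the wrong one, so it needs correcting even if arm was meant.

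Second, the article does provide for missing data through EM and Heckman methods and a comparison of withdrawals with completers. This stands against any claim that the plan discards participants: no section says so. What remains is that these provisions are not connected to the MANCOVA.

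Third, these scales are not the outcome of the primary or secondary aim, and the mediation analysis uses structural equation or causal mediation models. This also stands, and it limits the weight of the point.

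A reader might go further and infer that follow-up loss is already tied to arm, because close-out follows a home study and 82 intervention against 52 control participants are expected. The article does not support this. It defines those numbers as people who complete every aspect of the trial, follow-up included. Nor does a loss rate that differs by arm by itself bias a covariate-adjusted comparison.

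**Conclusion.** The point holds as a correction to a supporting analysis. As worded, the questionnaire analysis tests change over time and cannot separate an intervention effect from a gain shared by both arms. Whether arm was intended cannot be settled from the article. The incomplete-data part is conditional: MANCOVA excludes partial responders by default, and the stated missing-data methods are not linked to it.

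The size depends on assumptions. If the 35% given for 6-month adherence data carries over to the questionnaires, between none and about 181 participants would be lost for lack of one visit, under the two patterns shown. It would be tempting to compare 258 with all 398 and read the difference as precision that a better model would recover. That is not supported: participants with no follow-up supply only a baseline value, and no model restores their outcomes. Bias is not demonstrated either.

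Separately, the close-out wording in the home-study section sits uneasily with Methods and design and with Exit interviews, which have everyone assessed at follow-up. Those passages need reconciling.

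**What to change.** Replace the MANCOVA sentence with a stated estimand: the between-arm difference at 6 months and at 12 months on each scale, adjusted for baseline, in all randomised participants. Estimate it per scale in a repeated-measures likelihood model with arm-by-time terms and allowance for clustering by educator, keeping participants who have only one follow-up visit. If a multivariate test is preferred, use a MANCOVA with arm as the factor and baseline as covariate, after an imputation procedure that is specified. In either case, say how the EM and Heckman provisions apply to these outcomes, or that they do not.

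Reconcile the close-out text with the two sections that have all participants complete the follow-up questionnaires, so that it is clear who is expected to provide them.

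The data are already scheduled for collection. The cost is plan wording and a little more programming. The model relies on data being missing at random, and one analysis per scale yields several univariate tests, which should be labelled as supporting.
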